***Secondary endpoints assessed in the intervention group only***		
TB detection by NPA testing	Proportion of NPA with positive TB detection using Ultra	After 1st visit
TB detection by Stool testing	Proportion of stool samples with positive TB detection using Ultra	After 1st visit
TB detection by NPA and Stool testing	Proportion of samples (NPA and/or stool) with positive TB detection using Ultra	After 1st visit
Turnaround time between NPA collection and result of Ultra	Date/Time of Ultra results – Date/Time of NPA collection	After 1st visit
Turnaround time between stool sample collection and result of Ultra	Date/Time of Ultra results – Date/Time of stool sample collection	After 1st visit
NPA collected as per protocol	Proportion of children with NPA collected as per protocol	At 1st visit
Stool samples collected as per protocol	Proportion of children with stool samples collected as per protocol	At 1st visit
Safety: adverse events (AEs) during NPA collection	Number of adverse events collected by study nurses during NPA collection including as vomiting, nose bleeding, low oxygen saturation	Any time during the follow-up
Tolerability: discomfort/pain/distress experienced by the child during NPA collection procedure	Assessed by the child him/herself (Wong-Baker face scale), by the parents (visual analog scale), by the nurses (FLACC behavioural scale)	At NPA collection time

*TB* tuberculosis, *NPA* nasopharyngeal aspirate

### Data analysis

We will perform final data analysis to answer the objectives at the end of the study after data review and database closure. At the request of the trial Independent Data Monitoring Committee (IDMC), an interim analysis on safety and feasibility data is planned at the point when all children enrolled during the first 9 months of the study have been followed for 12 weeks; there are no stopping rules planned and no formal statistical test will be used. We will conduct a descriptive analysis of the endpoints and other measured variables and characteristics (Table 6). Quantitative variables will be summarized using means, standard deviation, median and interquartile range. Categorical variable will be analysed using frequencies and proportions.

The analysis of the primary endpoint will be performed following an intention-to-treat principle. Patterns of missing values will be analysed but no imputation will be done. As the literature regarding statistical analysis of stepped wedge designs is constantly growing, we will follow the recommendations of Hemming and colleagues [28], using the Hussey and Hughes model for the primary analysis [29]. Thus, we will used generalised linear mixed models with logit link and binary distribution. We will model individual binary response (vital status) with condition (control vs intervention) and time-period as fixed effects and sites as random effects to adjust for clustering of children. Sensitivity analyses will be performed to control for 1) important prognostic factors such as age, malnutrition, HIV infection, severity criteria measured at recruitment, 2) seasonality which could be different in different countries and, 3) different model specifications to better adjust secular trends and cluster heterogeneity [28]. These model specifications are developed and detailed in a statistical analysis plan that will be validated by the IDMC before performing the analysis. All results will be reported as estimates of effect (odds ratios for binary variables) and corresponding 95% confidence intervals. We will conclude that the intervention is better than the control if the mortality odds ratio is statistically lower than 1 (*p* < 0.05).

All analyses will be performed using R (version 3.6.0 or higher) and findings will be reported as per the CONSORT extension for reporting of stepped-wedge cluster-randomized trials [30].

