### Endpoints

#### Primary study endpoint and measure

The primary endpoint is all-cause mortality 12 weeks after recruitment. Mortality due to severe pneumonia (related or not to TB) is expected to occur early. We expect that a 12-week period is long enough to assess impact on mortality of TB treatment empirically started in children with poor clinical progress during the first weeks of follow-up. If the children are not brought to the Week 12 visit, parents will be contacted, and home visits will be organized in order to collect the vital status of the child.

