***Secondary endpoints considered for a comparison between arms***		
TB diagnosis based on the clinician’s judgement	# of children diagnosed with TB based on the clinician’s judgement	Any time during the follow-up
TB treatment initiation	Proportion of children diagnosed with TB AND who with at least one TB treatment recorded	Any time during the follow-up
Time to TB treatment initiation	Date/Time of the 1st TB treatment – Date/Time of TB diagnosis (in hours)	Any time during the follow-up
Duration of TB treatment at end of trial	Number of days between date of TB treatment initiation and date of TB treatment end	Any time during the follow-up (week 12 or early termination)
Inpatient deaths	# of children who died after inclusion and before hospital discharge	Before discharge
Duration of initial hospitalization	Date of the 1st recorded discharge – Date of the 1st recorded admission (in days)	At the first discharge
Readmission following discharge	# of admission occurring after the 1st discharge	Any time during the follow-up
Weight gain	Proportion of weight gain at 12 weeks (as compared to body weight at inclusion)	At 12 weeks
Cost effectiveness	Incremental cost-effectiveness ratio (ICER) of intervention compared with WHO SOC, measured in cost per DALY averted	Lifetime, based on differences in mortality up to 12 weeks

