### Power and sample size

Sample size calculations were performed based on several assumptions. (1) The expected proportion of TB cases in children with pneumonia would be 15 and 24%, in high and very high incidence settings, respectively, with a proportion of 33% of culture confirmed cases among TB cases overall (2). In the context of our intervention, Ultra could detect the majority of confirmed TB cases, versus a hypothesized TB detection rate of 25% in routine conditions. (3) The intervention would raise awareness about TB in site clinicians and would lead to an increase in detection rate from 15 to 50% between the control and the intervention arm. (4) We estimate that in the control arm the overall mortality will reach 15%, in line with mortality associated to severe pneumonia in previous studies, and that the intervention would therefore lead to a 30% reduction in the overall mortality rate (10.5%).

According to these assumptions, the sample size for an individual randomized trial would be 1730 children. For financial and logistical reasons, we retained an ICC value of 0.005, corresponding to a design effect of 2.16 [31]. Using the estimated mortality of 15% in the control arm, an expected reduction in mortality in the experimental arm of 30%, an alpha of 0.05, a power of 80%, an ICC of 0.005 and 1% of incomplete data, the corresponding sample sizes would be 3780 children. This sample size randomised across the two strategies, in 15 hospitals over 16 periods, resulted in a mean of 15.8 children enrolled per hospital per time period (or 252 children per hospital for the entire study), with no restriction if included numbers exceed this target.

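### No listed sensitivity analysis covers unknown week-12 vital status, and stay, readmission and weight gain are compared between arms in groups that mortality itself selects

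*Protocol article*

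**What the plan says.** **Primary endpoint.** The section on the primary endpoint states: "The primary endpoint is all-cause mortality 12 weeks after recruitment". If a child is not brought to the last visit, "parents will be contacted, and home visits will be organized in order to collect the vital status of the child". The Data analysis section adds: "The analysis of the primary endpoint will be performed following an intention-to-treat principle", followed by "Patterns of missing values will be analysed but no imputation will be done". The model is a logistic mixed model: "We will model individual binary response (vital status) with condition (control vs intervention) and time-period as fixed effects", with site as a random effect. Three groups of sensitivity analyses are named: adjustment for prognostic factors, seasonality, and alternative model specifications. Only the last is expressly left to the statistical analysis plan. The Power and sample size section assumes "an ICC of 0.005 and 1% of incomplete data".

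**Secondary endpoints.** Table 6 lists these among the endpoints to be compared between arms:
- duration of initial hospitalization: "Date of the 1st recorded discharge – Date of the 1st recorded admission (in days";
- readmission: a count of admissions after the first discharge, at any time in follow-up;
- weight gain: "Proportion of weight gain at 12 weeks (as compared to body weight at inclusion".

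Inpatient death is a separate between-arm endpoint in the same table, defined as death after inclusion and before discharge.

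**The concern.** There are two separate problems.

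The first concerns children whose vital status at week 12 is never established. With a binary response and imputation ruled out, they contribute nothing, so the analysis called intention to treat is a complete-case analysis. The Background stresses that risk of death stays high in the three months after discharge, so loss may be related to death. Retention could also differ by arm. TB drugs are dispensed at follow-up visits, and the plan expects more TB to be detected under the intervention, so more intervention families may have a reason to return. That is inference, not something the article states. The Discussion argues that mortality carries no ascertainment bias because it is not subjective, but an objective endpoint can still be incompletely ascertained.

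The second does not need any loss to follow-up. Three secondary comparisons use measures that death can prevent from existing, and the trial's hypothesis is that the intervention reduces death. If it does, the intervention arm includes children who would have died under control, probably frailer than average. Stay, readmission or weight gain could then look worse in the better arm without any harm having been done.

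**Working it through.** **1. The plan's own sample size.** Inputs from Power and sample size: 15% against 10.5% mortality, alpha 0.05 (taken as two-sided), power 80%, design effect 2.16, 1% incomplete data.

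n per arm = [1.960·√(2 × 0.1275 × 0.8725) + 0.842·√(0.15 × 0.85 + 0.105 × 0.895)]² / 0.045² = 862, so 1724 in total against 1730 stated.

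1730 × 2.16 = 3736.8, and 3736.8 / 0.99 = 3775 against 3780 stated. The figure reproduces, and 1% is the only missing-data rate in the article.

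**2. Effect of unknown vital status on the primary odds ratio.** Let p be true mortality in an arm, m the fraction with unknown status, and k the mortality of those children relative to the observed ones. Then

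observed mortality = p / [(1 − m) + m·k].

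The planned odds ratio is (0.105/0.895) / (0.15/0.85) = 0.665. Values of m above 1% and all values of k are assumptions. The comparison is a simple two-arm one that ignores site and period. Each range below runs from k = 2 to k = 3.

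| Loss, control / intervention | True OR 0.665 | True OR 1 |
|---|---|---|
| 1% / 1% | 0.665 to 0.666 | 1.00 |
| 5% / 5% | 0.667 to 0.668 | 1.00 |
| 10% / 10% | 0.668 to 0.671 | 1.00 |
| 5% / 2% | 0.689 to 0.711 | 1.03 to 1.07 |
| 10% / 5% | 0.704 to 0.739 | 1.06 to 1.11 |
| 2% / 5% | 0.644 to 0.626 | 0.97 to 0.94 |

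One cell written out (5% / 2%, k = 3, no effect): control 0.15/1.10 = 13.64%, intervention 0.15/1.04 = 14.42%, odds ratio 1.07.

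Equal loss barely moves the estimate. Unequal loss can bias it in either direction.

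Power is a lesser matter. The Hussey and Hughes variance (linear approximation, 15 × 16 layout, 15.75 children per cell) gives 80.1% at 1% missing, 78.7% at 5% and 76.9% at 10%.

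**3. Weight gain.** Table 1 has 120 control and 120 intervention cells. With equal cell sizes that is 3780 / 2 = 1890 children per arm. A 12-week weight can exist for at most 1890 × 0.85 ≈ 1607 control and 1890 × 0.895 ≈ 1692 intervention children. The two survivor groups differ by 4.5 points.

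As an illustration, let the frailest children die, let frailty be standard normal, and let it correlate r with weight gain. Survivors-only means then differ by r × 0.071 SD with no effect on weight, which is 0.02 to 0.04 SD for r = 0.3 to 0.5 (assumed).

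**4. Stay and readmission.** Table 6 places inpatient death before discharge and measures stay to a discharge date. It supports two readings. Either a child who dies in hospital has no stay value, or the date of death closes the record and an early death counts as a short stay. The first compares selected groups, and the second scores death as a favourable outcome. Readmission requires a live first discharge, so it is selected by inpatient death only. The size for stay and readmission cannot be computed: the planned 15% and 10.5% are 12-week figures and are not split into inpatient and later deaths. The inpatient range cited in the Background (8.7 to 32%) comes from other studies and is not by arm.

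**The case against.** **What a reader might infer, and why the article does not support it.**
- That children who die are dropped from the primary analysis. They are not: death is the primary event and vital status is the modelled response, so every known death counts.
- That readmission exists only for 12-week survivors. A child who is readmitted and then dies still contributes.
- That stay would lengthen by 0.35 to 0.65 days. This comes from (85 × 7 + 4.5 × 14)/89.5 − 7 = 0.35 and (85 × 7 + 4.5 × 20)/89.5 − 7 = 0.65. It assumes stays of 7 days for most children and 14 to 20 for the extra survivors, and treats every 12-week death as an inpatient death. The article gives none of these.
- That each 1% of unknown status can move an arm's mortality by 0.85 points (0.99 × 0.15 + 0.01 − 0.15). This is a bound that needs every untraced child in that arm to have died.

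**The case for the plan.** Families are contacted and visited at home to obtain vital status, and at the 1% allowed for, the bias is trivial. Patterns of missing values will be analysed. The covariate-adjusted sensitivity model is valid if missingness depends only on the variables in that model, and imputation from the same baseline variables would add little. The no-imputation sentence sits in the primary-endpoint paragraph and sets no rule for Table 6. Handling of death in secondary endpoints often belongs to the analysis plan, which is not shown. Inpatient death is itself compared between arms, so stay can be read beside it.

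**What stands.** Most of this limits the size of the primary problem. It does not remove it: the covariate-adjusted model omits the same children, and describing patterns does not show how far the result depends on them. For Table 6, the finding is not that the article omits detail. The measures it states, assigned to a between-arm comparison, depend on an outcome the intervention is meant to change.

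**Conclusion.** The point holds in a limited form, and the plan should be changed.

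For the primary endpoint, the stated rule gives a complete-case analysis with no listed check on unknown vital status. The likely bias is negligible at 1% loss or with equal loss. It becomes material only with larger and unequal loss. The 1.07 and 0.94 examples under no effect rest on assumed 5% and 2% loss and threefold risk, and they show that the direction is not known in advance.

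The secondary problem is the firmer one because it follows from Table 6 and the planned effect alone. Weight gain is restricted to at most 85% against 89.5% of children. The resulting bias in mean weight gain may be small (0.02 to 0.04 SD in the illustration). Stay is either undefined or shortened by inpatient death, and readmission is conditional on live discharge. For these two the problem is established, but its size cannot be computed from the article.

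**What to change.** **Primary.** Keep the stated mixed model as the primary analysis. Limit the no-imputation rule to it, and pre-specify two sensitivity analyses for missing vital status:
- multiple imputation including arm, time-period, site and baseline covariates. Time-period must be included because in a stepped wedge it is correlated with condition;
- a tipping-point analysis varying mortality among untraced children separately by arm. This is the more informative of the two, since it does not rely on measured covariates explaining the loss.

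Report the number with unknown status by arm.

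**Secondary.** Analyse stay as cumulative incidence of discharge alive with death as a competing event. Treat death as a competing event for readmission. Report weight gain as descriptive in survivors, or as a composite that ranks death worst. Days alive and out of hospital should be used only if readmission dates were collected, since Table 6 promises only a count.

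**Cost.** Wording in the analysis plan, which the data monitoring committee validates before the analysis, some extra programming, and slightly less simple secondary estimates. No new visits are needed. The planned last visit was December 2020, so the additions must use data already collected.

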In high TB burden settings, there is growing evidence that TB is common in children with pneumonia [9]. Although TB is a chronic disease in adults, recent data shows that the duration of respiratory symptoms before admission can be acute in children with severe pneumonia associated with TB [10]. A systematic review showed that up to 23% of children admitted to hospital with an initial diagnosis of pneumonia were later diagnosed with TB [10, 11]. This is particularly true in the African and South-East Asian WHO regions, which accounted for 30 and 40% of all paediatric TB cases in 2019 respectively [1]. In these regions, the case fatality rate for childhood pneumonia associated with TB is high, ranging from 4 to 21% [10], with younger age, malnutrition and HIV infection increasing the risk of death [12, 13]. However, the diagnosis of TB in children with severe pneumonia remains low. Indeed, the current WHO standard of care (SOC) for young children with pneumonia considers a diagnosis of TB only if the child has a history of prolonged symptoms or fails to respond to antibiotics [14]. Therefore, many children with TB-associated severe pneumonia are currently missed or diagnosed too late, which is likely to affect their outcome.

In 2013, WHO updated its policy to include Xpert MTB/RIF (Cepheid, USA) as the initial test for the diagnosis of TB in children, based on a meta-analysis showing a pooled sensitivity and specificity of Xpert MTB/RIF performed on gastric lavages of 66% (95% confidence interval 51–81) and 98% (95% confidence interval 96–99), respectively, when compared with culture [15, 16]. Although data on the performance of Xpert MTB/RIF in children with pneumonia are limited, in Bangladesh, sensitivity on gastric aspirates or sputum samples compared to culture in this group was equivalent to that reported in other studies [17]. The next-generation of Xpert MTB/RIF assay, Xpert MTB/RIF Ultra (Ultra), has a lower detection threshold (similar to culture), which is expected to improve the diagnosis of children with paucibacillary TB [18, 19].

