### Randomisation

Randomisation is stratified by the estimated country TB incidence rate, classified as either high (100 to < 300/100,000 patients-years; Cameroon, Côte d’Ivoire and Uganda) or very high (≥ 300/100,000 patients-years; Cambodia, Mozambique and Zambia) [9] (Table 1). Within these strata, a computer-generated random sequence will determine the order in which hospitals move from control to intervention. The statistician of the international coordination team, based at University of Bordeaux, will prepare the randomization sequence before the start of the trial.

The time when a new cluster receives the intervention is called a step. In the TB-Speed Pneumonia study, the period between two successive steps is 5 weeks (Table 1). The international coordination team and country research teams are blinded to the randomisation order. The international coordination team however is informed 10 weeks in advance (i.e. two periods) of the next site to switch, while study sites are notified 5 weeks prior to their crossover date to initiate program planning.

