### Study visits and assessments

After written informed consent is obtained from parent(s)/guardian(s) by the study clinician or study nurse, the baseline visit includes a complete clinical evaluation, a digitalized chest X-ray (CXR), HIV and malaria testing, and a complete blood count. For children in the intervention arm, initial bacteriological specimen collection is done as soon as possible and within 24 h of hospital admission, including one NPA collected by the nurse on the day of admission, and one stool sample collected as soon as the child is able to produce stool. Additionally, blood samples and leftovers from NPA and stool are collected for future biomarkers studies in children for whom parent(s)/guardian(s) give their consent for biobanking. Data about routine care as well as additional study strategies are collected. All children are followed up for a total duration of 12 weeks, with four systematic protocol visits planned at day 3 (and/or at hospital discharge), 2 weeks after discharge (as recommended by the WHO SOC), and 12 weeks after recruitment. Each follow-up visit comprises a clinical evaluation, and collection of medical history since the last visit, an evaluation of adherence to TB treatment if initiated, and TB drug prescription and dispensation to cover the time until the next visit (Table 5). Parent(s)/guardian(s) are invited to bring their child back to the hospital in case of new symptoms for an unscheduled (extra) visit. During the final visit at 12 weeks, a second digital CXR is performed, as well as an assessment of TB disease evolution and TB treatment outcome in those diagnosed with TB (improvement, treatment failure, death, or lost to follow-up).

**Table 5 Tab5:** Study assessments and specimen collection

	Inclusion (Day 0)	Day 3	Discharge	2 Weeks Post-Discharge	(Extra visit)^**i**^	Week 12

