### Strengths and challenges of the stepped-wedge design

The stepped wedge design is particularly relevant where it is predicted that the intervention will ultimately do more good than harm, as is the case for our intervention, but where there is uncertainty as to its effectiveness and its safety in a specific setting and population [40]. The choice of the stepped wedge design was also based on our hypothesis that the intervention would raise TB awareness among clinicians and may lead to more empirical TB treatment initiated in the intervention arm as compared to the control arm, thus benefitting all children hospitalized, and impacting beyond the research settings. Since clusters are expected to remain until the study ends, they will all eventually implement the intervention. The stepped-wedge design is therefore particularly adapted to capture such effects. From a logistical point of view, a phased roll-out of the intervention is easier to implement in the context of an international multicentre study. Randomisation per hospital is also advantageous due to the difficulty at health facility level of randomising children individually to one of the two strategies, additionally minimising contamination between the two arms.

A major limitation of stepped wedge designs is that blinding of the study team to the intervention is not possible. However, since the primary trial endpoint (mortality at 12 weeks) is not subjective, there is no risk of ascertainment bias. As the intervention relates to the management of children upon hospital admission, outcomes are estimated only from individuals with no prior exposure to the control, thus avoiding carryover (residual) effect [41]. Moreover, in order to guarantee that children benefit from the same quality of care across study sites, adherence to WHO SOC for severe pneumonia will be monitored throughout the study implementation.

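### The primary mortality model omits the randomisation stratum and the baseline prognostic factors, although unblinded staff enrol after the arm is known; including them would bring a modest gain in power and protection against measured case-mix shift

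*Protocol article*

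**What the plan says.** All references are to the protocol article.

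- **Primary model (Data analysis):** "We will model individual binary response (vital status) with condition (control vs intervention) and time-period as fixed effects and sites as random effects". The superiority conclusion is an odds ratio below 1 at p<0.05.
- **Covariates (same section):** "Sensitivity analyses will be performed to control for 1) important prognostic factors such as age, malnutrition, HIV infection, severity criteria measured at recruitment". Seasonality and other model specifications are further sensitivity analyses, to be detailed in a statistical analysis plan. No imputation is planned.
- **Stratum (Randomisation):** "Randomisation is stratified by the estimated country TB incidence rate", in two classes, high (8 hospitals) and very high (7 hospitals). No analysis mentions it.
- **Prognosis (Background):** in childhood pneumonia associated with TB, fatality is high, "with younger age, malnutrition and HIV infection increasing the risk of death".
- **Knowledge of the arm (Randomisation):** "study sites are notified 5 weeks prior to their crossover date to initiate program planning". The section on strengths and challenges adds: "A major limitation of stepped wedge designs is that blinding of the study team to the intervention is not possible".
- **Enrolment (Study visits and assessments):** the baseline work-up begins "After written informed consent is obtained from parent(s)/guardian(s) by the study clinician or study nurse". Table 5 lists the nasopharyngeal aspirate and stool sample for the intervention arm only.

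**The concern.** Randomising the order in which hospitals switch balances the arms only if the children enrolled before and after each switch are comparable. Here enrolment follows knowledge of the arm, and parents consent to different procedures in the two arms. Staff or parents could hesitate over the sickest children once sampling is part of the package, or enrolment could widen. The site term removes only stable differences between hospitals, and the period term only time trends common to all of them. A change in case mix that coincides with each hospital's own switch passes straight into the estimated intervention effect, in either direction.

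The article's answer to the lack of blinding is that death is not subjective. That concerns how the outcome is ascertained, not who enters the trial. The factors that would reveal and partly correct a shift are collected in both arms at inclusion. If the planned and the adjusted models disagree, the article's decision rule does not say that the adjusted one counts.

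**Working it through.** **1. The plan's own figures.** Inputs from Power and sample size: mortality 15% and 10.5%, alpha 0.05 (taken as two-sided), power 80%, ICC 0.005, 15 hospitals, 16 periods, 1% incomplete data.

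- Individual trial: n per arm = [1.96√(2p̄q̄) + 0.842√(p₁q₁+p₂q₂)]² / 0.045² with p̄ = 0.1275. This gives 862 per arm, 1724 in total (stated 1730).
- Stepped-wedge design effect (Woertman), k = 15 steps, one baseline period, n = 3780/(15×16) = 15.75 per cell: [1+0.005×251]/[1+0.005×132.875] × 3×0.995/[2(15−1/15)] = 0.1354. Times 16 periods = 2.167 (stated 2.16).
- Total: 1730 × 2.16 / 0.99 = 3775 (stated 3780).

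The sample size is sound. It assumes no covariates.

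**2. Power with covariates.** Hussey-Hughes variance for the Table 1 layout: Var = I·s(s+Tτ²) / [(IU−W)s + (U²+ITU−TW−IV)τ²], with I = 15, T = 16, U = 120, W = V = 1240. So IU−W = 560 and the last bracket is 4760. Total variance is 0.1275×0.8725 = 0.1112, τ² = 0.005×0.1112, and s is the within-cell variance divided by 15.59 children (15.75 less 1%). Power = Φ(0.045/SE − 1.96). Covariates are represented by shrinking the within-cell variance by an assumed share.

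| Outcome variance explained (assumed) | SE | Power |
|---|---|---|
| 0% | 0.01604 | 80.1% |
| 5% | 0.01569 | 81.8% |
| 10% | 0.01534 | 83.5% |
| 15% | 0.01498 | 85.2% |

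This is a linear shortcut for a logit model. A simulation of the logistic random-intercept model (600 trials per scenario, error about 1.6 points) agrees in size. With no stratum difference and a prognostic score of SD 1.0 on the logit scale, power was 80% for the planned model and 84% with stratum and score. A weak score (SD 0.5) added nothing beyond the stratum.

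**3. The stratum.** In Table 1 both strata average 8.0 of 16 periods on intervention, and the site effect absorbs differences in level. Omission therefore causes no bias. In the simulation, adding the stratum gained 0 points with equal stratum mortality, about 3 at a log-odds difference of 0.4, and about 6 at 0.8.

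**4. Size of a possible selection bias (assumption).** Suppose the intervention does nothing, but 10% of children who would die are not enrolled after the switch. Observed mortality is 0.15×0.9/(0.15×0.9+0.85) = 0.135/0.985 = 13.7%. The odds ratio is 0.90 and the difference 1.3 points, or 29% of the 4.5-point target.

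**5. Shift in a measured score (assumption).** The same simulation with no true effect, score SD 1.0 and stratum log-odds difference 0.4, counting false findings of benefit (nominal 2.5%):

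| Children less ill after the switch by | Planned model | Adjusted model |
|---|---|---|
| 0.1 SD | 8.2% | 2.0% |
| 0.2 SD | 20.7% | 2.2% |

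With score SD 0.5 and a 0.1 SD shift, the rates are 4.0% and 2.7%. The adjusted model does well here by construction, because only the measured score was shifted.

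**The case against.** Adjustment for the same factors is already planned as a sensitivity analysis, and an unadjusted Hussey-Hughes primary model is a recognised choice. Any child with presumptive severe pneumonia is to be screened, against fixed WHO criteria with one exclusion, and with no cap on numbers sites have no quota that forces them to choose. This stands: nothing in the plan is miscalculated, and these safeguards lower the chance of selection. They do not remove it, because individual consent still follows knowledge of the arm, and the planned sensitivity analysis has no part in the decision rule.

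Four stronger readings are tempting and not supported:

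- *That omitting the stratum biases the result or pushes power below 80%.* The layout is balanced, so there is no bias. The simulated 74-77% for the planned model arises mostly because the stratum difference was added on top of a site variance already set at ICC 0.005. Differences of 0.4 and 0.8 raise the total ICC to about 0.010 and 0.025, at which closed-form power is 76.5% and 72.6%. That is a departure from the planned ICC more than a fault of the model.
- *That adjustment would remove the odds ratio of 0.90.* That example selects on the outcome itself. Covariates remove only the part they carry.
- *That the article denies all bias from lack of blinding.* Its statement is already limited to ascertainment. It is silent on enrolment.
- *That adjustment is free.* With no imputation, a complete-case adjusted model would drop children lacking HIV status or severity data, and because deaths are expected early, that missingness could be related to death.

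**Conclusion.** The concern holds, at modest size. The primary model and its decision rule leave unused a randomisation stratum and prognostic factors that the trial already collects, in a design where enrolment follows knowledge of the arm. The expected gain is power of about 80% rising to 82-85%, if covariates explain 5-15% of outcome variance, and protection against shifts in measured factors only. Prognostic strength, stratum difference and shift size are all assumptions, because the article gives none.

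A reader might infer that case mix did shift, or that the trial's result will be biased. The article shows a route for selective enrolment and nothing more. Adjusted results will be reported in any case, so this is a recommended improvement, not a fatal flaw.

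**What to change.** - Make primary the mixed logistic model with TB-incidence stratum, age, severe malnutrition, HIV status and admission severity as fixed effects, plus the period and site terms. Tie the p<0.05 conclusion to it, and keep the unadjusted Hussey-Hughes model as a sensitivity analysis.
- State a rule that keeps children with missing covariates in the intention-to-treat analysis, for example a missing-category indicator, since no imputation is planned. Report the amount missing by condition.
- Give a standardised risk difference beside the odds ratio, because the adjusted odds ratio is conditional on the covariates and lies further from 1 (in the simulation, log odds ratio −0.45 against −0.41).
- Report baseline severity by condition, and say in the discussion of blinding that an objective endpoint does not address selective enrolment.

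No new data are needed. The cost is a documented change to a primary model that the article already states, not just wording in the analysis plan. Recruitment was due to end in September 2020 and the article appeared in March 2021, so the change must be dated and justified before the analysis, at the point where the data monitoring committee validates the analysis plan.
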